#### Recruitment

The study is being conducted at 3 university hospitals (Lille, Amiens, Caen) in the northwest area of France as part of the university communities (*InterRégional*). Patients are referred by their general practitioner to a psychiatric consultation service for psychological treatment of anxiety symptoms in a context of recent stress. To improve recruitment, general practitioners in the 3 areas were informed of the study by a local investigator during continuing medical education, during scientific meetings, and through all types of collaborative contacts between primary care and psychiatry services. We also directly informed the general practitioners who were involved in previous research on ADA and CBT and invited them to refer patients.

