#### Randomization

Immediately after inclusion and assessment, patients are randomly allocated in a 1:1:1 ratio into 3 groups using a Web-based central randomization: patients using a digital stress management module (group 1), patients following the stress management module guided by a therapist in attendance (group 2), and patients on a waiting list and benefiting from usual care through their attending physician (group 3).

The randomization sequence is provided by an independent statistician (who does not take part in assessing the patients at any point in the study) using computer-generated random numbers with block sizes of 6 and center stratification consistent with the Consolidated Standards of Reporting Trials (CONSORT) [48]. The randomization sequence is implemented in the electronic case report form (eCRF) system to ensure a centralized, real-time randomization procedure.

A document describing the randomization procedure is kept confidential in the Clinical Investigation Centre of Lille University Hospital.

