### Statistical Analysis

#### Overview

Statistical analysis will be conducted in a blinded fashion with a blinded code for the intervention. All statistical analyses will be carried out independently in the Department of Biostatistics of the University Hospital of Lille. SAS 9.3 (SAS Institute Inc) software or later will be used. *P* values will be reported as the actual values, unless *P*<.001. No interim analyses are planned. A detailed statistical analysis plan (SAP) will be drafted and validated before the database is frozen. Patient characteristics at baseline will be described for each of the 3 arms; the quantitative variables will be described either by the mean and standard deviation in case of a Gaussian distribution or by the median and interquartile range if not. The normality of the distributions will be verified graphically by histograms and by the Shapiro-Wilk test. The qualitative variables will be described by the numbers and percentages of each category. All analyses for the primary and secondary objectives will be performed on all randomized patients in their original group of randomization according to intention-to-treat (ITT) principles. No subgroup analysis will be performed.

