#### Main Objective

Comparison of the primary endpoint (2-month change in STAI scale) between each experimental group and the control group will be performed separately using an analysis of covariance with an adjustment for the STAI baseline value and the center. Since 2 comparisons will be made for the primary analysis, each of them will be performed at the 2.5% significance level (Bonferroni correction). The absolute mean differences and effect sizes (standardized mean difference) will be reported with the 95% confidence interval. In case of deviation from normality of model residuals, nonparametric analysis will be used; absolute changes between baseline and 2-month visits will be calculated and compared between the experimental arm and control arm using nonparametric analysis of covariance adjusted for baseline values [63,64]. The primary analysis will be conducted according to the ITT principle. Missing values will be handled by multiple imputation procedures. Missing data will be imputed under the missing at random assumption using a regression switching approach (chained equation with m=20 imputations) with predictive mean matching method for continuous variables and logistic regression (binary, ordinal, or polynomial) for qualitative variables [65]. The imputation procedure will be performed using the main baseline characteristics, outcome, and variable group of randomization, and multiple imputed data sets will be combined using Rubin’s rules [66,67]. Sensitivity analyses will first be conducted using all available STAI measurements (complete cases analysis) and second in patients without major deviation from protocol (per protocol analysis); major deviations will be specified in the SAP.

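### The nonparametric fallback for the primary endpoint is adjusted for baseline only and leaves out center, the stratification factor that the primary ANCOVA includes

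*Protocol article*

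**What the plan says.** Under Main Objective, the 2-month change in STAI is compared between each program and the control group "using an analysis of covariance with an adjustment for the STAI baseline value and the center". The section promises an estimate on the mean scale: "The absolute mean differences and effect sizes (standardized mean difference) will be reported with the 95% confidence interval". The next sentence sets a replacement: "In case of deviation from normality of model residuals, nonparametric analysis will be used". Changes from baseline are then compared between arms "using nonparametric analysis of covariance adjusted for baseline values". Center is not named for this replacement.

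Under Randomization, allocation is done "using computer-generated random numbers with block sizes of 6 and center stratification". The Recruitment section lists three university hospitals.

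Under Secondary Objectives, six scores at 2 months (HADS anxiety, PSWQ, VAS-stress, PSS, BDI, HADS depression) follow the primary method, so they inherit the fallback. The 6-month mixed model against control does name center.

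**The concern.** The two versions of the same confirmatory test use different covariates. Center is in the version used when residuals look normal and out of the version used when they do not. Nothing about non-normal residuals is a reason to drop a stratification factor.

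Stratified blocks make the arms nearly balanced within each hospital. Differences between hospitals therefore add almost nothing to the true variance of the treatment contrast. An analysis that omits center still counts those differences as noise. Its standard error is too large, its real type I error falls below the nominal 2.5%, and power is lost. At stake is avoidable power in a trial sized for 80% with 32 evaluable patients per arm, in exactly the case where the fallback is used.

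**Working it through.** **The plan's own figure.** Inputs from Sample Size: difference 11.5, SD of change 14.6, alpha 2.5% (taken as two-sided), power 80%.

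- Normal approximation: n = 2 × (2.241 + 0.842)² × (14.6/11.5)² = 2 × 9.505 × 1.612 = 30.6, so 31 per arm. The exact t calculation gives 32 (power 80.1%).
- 32/0.8 = 40 per arm, and 3 × 40 = 120.

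The stated size reproduces and is not in question. It sets the 32 per arm used below.

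**Why omitting center is conservative.** Residual SD after baseline adjustment, with the plan's correlation of 0.5: 14.6 × √(1 − 0.5²) = 12.64, variance 159.8. Assume center shares of 50/25/25 and center shifts of −k, 0, +k. The between-center variance is 0.75k² − (0.25k)² = 0.6875k². With balanced arms, the standard error without center is too large by √(1 + 0.6875k²/159.8). The real two-sided error is then the tail beyond 2.241 times that factor:

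| k | Between-center variance | SE factor | Real error (nominal 2.5%) |
|---|---|---|---|
| 2 | 2.75 | 1.009 | 2.4% |
| 5 | 17.2 | 1.052 | 1.8% |
| 8 | 44.0 | 1.129 | 1.1% |

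**Simulation of the fallback with and without center.** Assumed: Quade-type rank ANCOVA, 32 per arm, the same center shares, residual SD 12.64, 4,000 replicates. Power is for a 9-point effect. The Monte Carlo standard error of the type I error is about 0.25 points.

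| Residuals | Center shifts | Type I error, without / with center | Power, without / with center |
|---|---|---|---|
| Normal | 0 | 2.3% / 2.4% | 68.0% / 69.2% |
| Normal | ±8 | 1.1% / 2.7% | 56.8% / 69.0% |
| Exponential | 0 | 2.7% / 3.0% | 85.4% / 86.3% |
| Exponential | ±8 | 0.8% / 2.2% | 67.6% / 80.5% |
| t, 3 df | 0 | 2.2% / 2.5% | 87.2% / 88.0% |
| t, 3 df | ±8 | 0.9% / 2.7% | 72.9% / 85.9% |

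The simulated error without center at ±8 (0.8% to 1.1%) agrees with the 1.1% from the formula. Omitting center costs 12 to 13 points of power at ±8 and about 1 point when centers do not differ.

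**Smaller center differences.** With gamma-skewed residuals and an 8-point effect, power without and with center is 62% v 69% at ±5 and 51% v 65% at ±8. At ±2 or less the gap is about 1 to 2 points.

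**The switch itself.** The article gives no trigger in this sentence. Shapiro-Wilk and histograms appear only in the Overview, for describing distributions. With an assumed trigger of Shapiro-Wilk P<.05 on the residuals, the switch fired in about 5% of trials with normal residuals, about 67% with t (3 df) and over 99% with exponential. Type I error of the whole two-stage rule was 0.9% to 2.7%.

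**The case against.** Several points stand against giving this more weight.

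- **Power of the plan as a whole.** The loss belongs to the fallback, not to the plan under normal residuals. There the fallback is rarely used, and the two-stage rule loses at most about 1 point to ANCOVA (56.8% v 57.7% at ±8, 8-point effect). With gamma residuals the plan as written equals or beats ANCOVA at 0 and ±5 (66.1% v 59.2%; 60.5% v 60.1%) and clearly loses only at ±8 (51.5% v 59.7%).
- **Size of the center effect.** A shift of ±8 is a 16-point spread between hospitals, wider than the planned 11.5-point treatment effect, and nothing in the article supports it. At the planned 11.5 points with ±5, the two-stage rule kept 89.7% power (normal) and 91.1% (gamma).
- **Further detail elsewhere.** The full protocol or the SAP may name center for the fallback. The trigger, and how it is applied across the 20 imputed data sets, are ordinary SAP detail and are not held against the plan.

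A reader might infer three stronger faults, which the article does not support. The first is that choosing the test from the residuals inflates type I error: the simulated rule did not exceed the nominal level beyond simulation error, the rule is written in advance, and the analysis uses a blinded intervention code. The second is that the fallback cannot give the promised mean difference. That would be true of a rank test, but the article never says the method is rank-based, and a randomization-based nonparametric ANCOVA can estimate an adjusted difference in mean change. The third is that ANCOVA must be the only primary test. That is a trade-off: with exponential residuals and ±8, the rank test with center had 80% power against 70% for ANCOVA.

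What remains is the mismatch in covariates. The article does list what the fallback adjusts for, and center is not there.

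**Conclusion.** The point holds as a minor one. The fallback for the primary endpoint, as described, omits the factor by which patients were randomized, while the ANCOVA it replaces includes it. The consequence is conservatism and lost power, not false positives: about 1 to 2 points of power at center shifts of ±2 or less, about 7 at ±5 (69 − 62) and about 14 at ±8 (65 − 51), under gamma residuals and an 8-point effect. These sizes rest on assumptions that the article does not give: a Quade-type test, the center shifts and the residual shape. The direction rests only on stratified allocation and some difference between hospitals.

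**What to change.** In the SAP, before the database is frozen, state that the nonparametric ANCOVA is adjusted for, or stratified by, center as well as baseline. Apply this to the primary endpoint and to the six 2-month secondary scores that use the same method.

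Add that the ANCOVA-adjusted mean difference with its confidence interval is reported whichever test supplies the P value, so that the promised estimate is available in either case.

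This takes a sentence or two and leaves the sample size of 120 unchanged. Making ANCOVA the only primary test, with the nonparametric analysis as a sensitivity analysis, is an option for the sponsor. It is simpler to prespecify but gives up some power if residuals are strongly skewed.

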#### Secondary Objectives

For the secondary endpoints of the HADS anxiety subscale, PSWQ, VAS-stress, PSS, BDI, and HADS depression subscale scores, comparisons of the changes between the baseline and the 2-month visit between each experimental group and the control group will be performed separately with the same methodology used for the primary endpoint.

Comparison of the change between the baseline and the 6-month visit for the primary endpoint and secondary endpoints between each experimental group and the control group will be performed separately using a linear mixed model. In this model, we will include the 2 measurements (at 2 and 6 months) for the time effect, the group effect (experimental/control), an adjustment for baseline values and center, and a time × group interaction. A contrast with a 2.5% type I error will be used to compare the 6-month change between the experimental and the control group.

The efficacy of the 2 therapeutic programs (face-to-face versus digital support) at 2 and 6 months will be compared using an analysis of covariance at the 5% significance level to compare the variations in the STAI score between the groups, adjusting for the baseline value.

VAS satisfaction and consumption of tobacco, alcohol, and drug use will be analyzed in each group using descriptive statistics.

The full version of the protocol can be viewed in Multimedia Appendix 4.

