### Adjustment Disorder With Anxiety

#### Definition

Adjustment disorder with anxiety (ADA) is the most frequent and best characterized stress-related psychiatric disorder [2]. According to the *Diagnostic and Statistical Manual of Mental Disorders, Fifth Edition* (DSM-5), a diagnosis of ADA is appropriate with the finding of anxiety occurring within 3 months of a psychosocial stressor or life event (eg, divorce, job loss, serious physical illness) [3] with symptoms generally abating by 6 months after the event. Considered a common disorder ranging from mild to moderate intensity, ADA is a true diagnostic entity. A general medical study showed that the level of anxiety is comparable to that of other anxiety disorders such as generalized anxiety disorder [4].

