#### Sample Size

In a study on the clinical and psychometric characteristics of ADA, the mean (standard deviation) of the STAI baseline score was 52.1 (SD 14.6) [4]. Two clinical studies with patients with generalized anxiety disorder, 1 comparing CBT with relaxation [61] and the other comparing CBT with brief psychodynamic psychotherapy [62], showed changes in the STAI-T scores of 7 and 16, respectively. In view of these results, we hypothesize that an average difference between each experimental arm and the control arm of 11.5 (the mean of 7 and 16). To demonstrate this difference in variation with a standard deviation of the STAI score change of 14.6 (assuming a conservative correlation coefficient of 0.5 between the baseline and 2-month STAI measures), a 2.5% type I error (using a Bonferroni correction for the 2 prespecified comparisons), and a power of 80%, it is necessary to include 32 patients per group. Although analysis of the primary outcome will be adjusted for baseline values, the sample size calculation does not take into account this adjustment to maximize the power. Finally, considering 20% ​​missing data, 120 patients (40 per group) are planned in this clinical trial.

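### The 6-month mixed model gives baseline one slope for both visits, which can bias the 6-month contrast slightly if that slope changes over time and dropout depends on baseline differently by arm

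*Protocol article*

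**What the plan says.** The Secondary Objectives part of the Statistical Analysis section sets out the 6-month comparison of each program with control. On the outcome side, "we will include the 2 measurements (at 2 and 6 months) for the time effect". The remaining terms are group, "an adjustment for baseline values and center, and a time × group interaction". The test is stated as follows: "A contrast with a 2.5% type I error will be used to compare the 6-month change between the experimental and the control group". The same model serves the STAI-T and six other scales (HADS anxiety, PSWQ, VAS-stress, PSS, BDI, HADS depression). With two comparisons each, that is 7 × 2 = 14 contrasts.

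Two other places bear on the point. Sample Size assumes a "correlation coefficient of 0.5 between the baseline and 2-month STAI measures" and gives no correlation for month 6. The Definition of the disorder in the Introduction describes "symptoms generally abating by 6 months after the event". Multiple imputation is described for the primary analysis and reaches the 2-month secondary scales by reference. For month 6 only the mixed model is named.

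**The concern.** Read literally, the listed terms force the regression on baseline to be the same at 2 and 6 months. If a patient's entry score predicts the 6-month score less well than the 2-month score, the fitted slope is a compromise that is wrong at both visits. Under randomization with complete data this is harmless on average, because the arms have the same expected baseline. The protection weakens when 6-month values are missing. A likelihood-based analysis under missing at random relies on a correct mean model, and arms that lose patients from different parts of the baseline range no longer have balanced completers.

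What is at stake is the claim in hypothesis 1 that the benefit over control is maintained at 6 months. The trial is open label with a wait-list arm, so dropout that differs by arm is conceivable. The article's own rules suggest one route, though this is inference. The discontinuation criteria release participants whose medication changes, while the control-arm description mentions stable medication only up to the 2-month assessment.

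**Working it through.** **The plan's own figure.** The article states no figure for the 6-month model, so the sample size was checked first.
- Inputs: difference 11.5, SD 14.6, correlation 0.5, two-sided alpha 0.025 per comparison, power 80%.
- SD of change = √(2 × 14.6² × (1 − 0.5)) = 14.6, as stated.
- The normal approximation gives 31 per group. The noncentral t gives power 0.787 at 31 and 0.801 at 32, which agrees with "a power of 80%, it is necessary to include 32 patients per group".
- 32 / 0.80 = 40 per group, and 3 × 40 = 120. The figures reproduce.

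**When bias arises.** Let b2 and b6 be the true baseline slopes and b the fitted common slope. Let λ be the fitted residual regression of month 6 on month 2. Let δ be, for each arm, the mean baseline of patients with a 6-month score minus that of all randomized patients. With month 2 fully observed:

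bias of the 6-month contrast = (δ_program − δ_control) × [(b6 − b) − λ(b2 − b)]

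The bracket is zero if b2 = b6. The first factor is zero with no dropout, or with the same dependence on baseline in both arms. Both must be nonzero for bias to arise. A baseline × time term fits b2 and b6 separately, so the bracket vanishes.

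**Assumed inputs.**
- b2 = 0.5, the article's correlation with equal SDs.
- b6 = 0.4, 0.3 or 0.2 (assumed).
- Correlation 0.6 between months 2 and 6 (assumed).
- 20% missing at month 6. The article's 20% is its allowance for the 2-month analysis and is borrowed here.
- Dropout logistic in baseline, log odds ratio 0.7 per SD (assumed).
- Center is left out.

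**Shift among completers.** For a normal baseline, the shift is 0.7 × E[p(1 − p)] / (1 − 0.20), where p is the dropout probability. Numerical integration gives E[p(1 − p)] = 0.148. The shift is 0.7 × 0.148 / 0.80 = 0.130 SD, and 0.130 × 14.6 = 1.90 points. If dropout depends on baseline in opposite directions in the two arms, the difference is twice that, 3.79 points before rounding.

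**Bias**, with b and λ taken from the fitted large-sample common-slope model:

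| b6 | b | λ | Bracket | One arm only (× 1.90) | Opposite directions (× 3.79) |
|---|---|---|---|---|---|
| 0.4 | 0.465 | 0.53 | −0.065 − 0.53 × 0.035 = −0.084 | 0.16 | 0.32 |
| 0.3 | 0.44 | 0.59 | −0.14 − 0.59 × 0.06 = −0.175 | 0.33 | 0.66 |
| 0.2 | 0.42 | 0.64 | −0.22 − 0.64 × 0.08 = −0.271 | 0.51 | 1.03 |

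These are absolute sizes. If the program arm loses its more anxious patients, the benefit is understated. If the control arm does, it is overstated. Direct large-sample fits gave 0.12, 0.30 and 0.48 (one arm) and 0.33, 0.65 and 1.09 (opposite). With equal slopes, or the same dependence in both arms, they gave 0 within simulation error. Stronger opposite dependence at b6 = 0.3 gave about 1.2.

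**Precision and error rate**, 3,000 simulated trials of 40 per arm, null true, alpha 2.5%:

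| Slopes at 2 / 6 months | Dropout | Common slope: bias, SD, rejection | With baseline × time: bias, SD, rejection |
|---|---|---|---|
| 0.5 / 0.5 | none | 0.00, 2.83, 2.1% | 0.00, 2.84, 2.2% |
| 0.5 / 0.3 | none | −0.01, 3.16, 2.4% | −0.01, 3.13, 2.5% |
| 0.7 / 0.4 | none | −0.03, 3.04, 2.4% | −0.05, 2.94, 2.0% |
| 0.5 / 0.4 | moderate, opposite | 0.29, 3.29, 2.6% | −0.03, 3.32, 2.4% |
| 0.5 / 0.4 | strong, opposite | 0.46, 3.29, 2.7% | −0.13, 3.41, 2.8% |
| 0.5 / 0.3 | moderate, opposite | 0.82, 3.38, 2.6% | 0.15, 3.37, 2.2% |
| 0.5 / 0.3 | strong, opposite | 1.18, 3.40, 2.8% | −0.01, 3.47, 2.3% |
| 0.7 / 0.4 | strong, opposite | 1.90, 3.40, 4.0% | 0.09, 3.39, 2.9% |
| 0.5 / 0.1 | strong, opposite | 2.35, 3.72, 5.1% | −0.05, 3.72, 1.9% |

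The simulation error of a 2.5% rate over 3,000 trials is √(0.025 × 0.975 / 3000) = 0.29 percentage points. Rates of 2.6 to 2.8% are therefore indistinguishable from nominal. With complete data the SD ratio (common slope to interaction) runs from 1.00 to 3.04 / 2.94 = 1.03. In the 0.5 / 0.4 rows with dropout the interaction is the less precise model, by 3.32 / 3.29 = 1.01 and 3.41 / 3.29 = 1.04.

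**The case against.** A common baseline slope is a conventional model and is valid under randomization with complete data. The article condenses a fuller protocol and announces a detailed analysis plan, and either could already enter baseline by visit. If the multiple imputation were carried to month 6 with baseline entering freely, the route to bias would largely close. This limits the point to a suggestion. It does not remove it, because the article gives an explicit list of terms, not an open description.

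A reader might infer that the model as written loses precision and yields a biased 6-month result. The article does not support that. The remark on abating symptoms concerns the average course and is timed from the stressor. It does not show that prediction from baseline weakens between the visits. The endpoint was chosen as a trait measure, which if anything suggests stability. Nothing in the article indicates baseline-related dropout that differs by arm. It reports one subject lost, with 50 of 120 participants enrolled. The precision loss is nil with equal slopes, at most about 3% with complete data, and can reverse under dropout. All of this stands.

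**Conclusion.** The point holds in a conditional and modest form. As listed, the model imposes one baseline slope. The 6-month contrast is biased only if the slopes differ between visits and dropout after 2 months depends on baseline differently by arm. For assumed 6-month slopes of 0.2 to 0.4 against 0.5, 20% dropout and moderate dependence, the bias is about 0.2 to 1.0 points. That is about 2% to 9% of the 11.5-point design difference (0.2 / 11.5 and 1.0 / 11.5), and small beside a standard error of 3.3 to 3.6. Type I error departs visibly from 2.5% (to 4.0% and 5.1%) only with large slope gaps and strong opposite dropout. The slopes, the correlation between visits and the dropout model are all assumptions. The primary 2-month analysis has a single visit and is not touched.

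**What to change.** Add a baseline × time interaction to the 6-month mixed model for the STAI-T and the six secondary scales, and keep the 6-month contrast at 2.5%. This can be written into the statistical analysis plan before the database is frozen. It needs no new data and no change in sample size. The cost is one degree of freedom and, if the slopes are in fact nearly equal, a standard error larger by about 1% in moderate scenarios and up to about 4% under strong differential dropout.

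### The digital versus face-to-face ANCOVA and the nonparametric fallback leave out center, the stratification factor that the other models include; if center is prognostic, these tests are slightly conservative

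*Protocol article*

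**What the plan says.** Under Randomization, the allocation list uses "block sizes of 6 and center stratification", with equal allocation to three groups at three university hospitals.

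Under Main Objective, each program is compared with the control group by ANCOVA "with an adjustment for the STAI baseline value and the center". If the residuals depart from normality, this is replaced by a "nonparametric analysis of covariance adjusted for baseline values"; center is not named there.

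Under Secondary Objectives there are three statements:
- The six other symptom scales at 2 months follow the method of the primary endpoint, so the same fallback applies to them.
- The 6-month comparisons with control use a mixed model that includes baseline and center.
- The two programs are compared at 2 and 6 months by ANCOVA at the 5% level "to compare the variations in the STAI score between the groups, adjusting for the baseline value". Again center is not named.

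No reason is given for the difference in covariates.

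**The concern.** Stratified allocation makes the arms nearly equal in size within each center. Differences between centers therefore largely cancel from the arm contrast, and its true variance does not contain them. A model without center still counts those differences as residual noise. If they exist, the reported standard error is larger than the true one, the test rejects less often than its nominal level, and power is lost.

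This bears most on the comparison of the two programs. The second item under Hypotheses expects them to be equally effective, and the planned analysis is a significance test. A standard error that is too large makes a nonsignificant result more likely, and a reader could take that result as support for the hypothesis.

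For the primary endpoint the issue arises only if the fallback is triggered. The covariates would then change along with the method.

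**Working it through.** **The plan's own figure.** The sample size does not depend on center, but it fixes the setting. The inputs under Sample Size are a difference of 11.5, an SD of change of 14.6 (14.6 × √(2 × (1 − 0.5)) = 14.6), a type I error of 2.5% taken as two-sided, and 80% power. The normal approximation gives 31 per group. The noncentral t calculation gives 32 (power 0.801 at 32, 0.787 at 31). Then 32 / 0.80 = 40 per group and 120 in total, as stated.

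**Closed form.** Let σ² be the residual variance after baseline adjustment, R² the share of it explained by center, and n the number per arm. With center balanced by the stratification:
- true variance of the arm difference: 2σ²(1 − R²)/n
- variance reported by the model without center: about 2σ²/n
- ratio of reported to true standard error: 1/√(1 − R²)
- actual size of a nominal two-sided 5% test: 2 × [1 − Φ(1.96/√(1 − R²))]

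R² is not in the document, so a range is assumed:
- R² = 0: ratio 1, size 5.0%
- R² = 0.05: ratio 1/√0.95 = 1.026, size 4.4%
- R² = 0.10: ratio 1/√0.90 = 1.054, size 3.9%

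**Simulation of the parametric ANCOVA.** Blocks of 6 were permuted within three centers of assumed sizes 48, 42 and 30. Two arms of 40 were compared with no missing data, an SD of 14.6 and a baseline to follow-up correlation of 0.5. There were 8,000 runs under the null and 4,000 for power at an illustrative 8-point difference. ICC is the assumed between-center share of residual variance. Each cell gives the result without center, then with center.

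| ICC | Mean reported SE | Size at nominal 5% | Power, 8 points |
|---|---|---|---|
| 0 | 2.83, 2.83 | 5.0%, 5.0% | 79%, 79% |
| 0.02 | 2.87, 2.84 | 5.1%, 5.4% | 77%, 78% |
| 0.05 | 2.90, 2.83 | 4.3%, 4.7% | 76%, 78% |
| 0.10 | 2.98, 2.84 | 3.9%, 4.9% | 77%, 79% |
| 0.20 | 3.16, 2.84 | 3.1%, 5.2% | 71%, 79% |

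The simulation error of a size near 5% is about √(0.05 × 0.95 / 8,000) = 0.24 percentage points, so the row for 0.02 shows no real departure from 5%. In the null runs the spread of the estimates themselves was 2.83 to 2.87 under either model. The estimate is about equally precise with or without center; what changes is the standard error reported for it. The ratios 2.90/2.83 = 1.02 and 2.98/2.84 = 1.05 agree with the closed form.

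The rank-based fallback was not simulated. The same direction is expected, but no figure is claimed for it.

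**The case against.** The strongest reply is that the loss is small and conditional. It vanishes if center does not predict outcome, and the document gives no sign of how much it does. Up to an ICC of 0.10 the power loss in the simulation is roughly 0 to 3 points. The 8-point loss needs an ICC of 0.20, which nothing in the article supports. This stands, and it makes the point a modest improvement.

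A second reply is that the article condenses a full protocol and precedes an SAP, neither of which is shown, and that center may be named there. This has some force for the fallback, which is described in one clause with references. It has less force for the program comparison, whose adjustment is written out beside models that do name center.

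Four stronger readings are tempting, and the document does not support them:
- A reader might infer that the standard errors are wrong in any case. They are too large only if center is prognostic.
- A reader might infer a likely center effect from the single assessing psychiatrist at each site. The primary scale is a self-report questionnaire that the psychiatrist collects and does not rate, so a rater effect does not follow. Other center differences are possible but undocumented.
- A reader might infer that the single-visit ANCOVA at 6 months is an error because the control comparisons use a mixed model. It is a valid analysis, and the choice between them is one on which statisticians differ.
- A reader might infer that the ANCOVA must stay primary whatever the residuals show. Switching methods on a residual check is a separate question from omitting center, and nothing here settles it.

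**Conclusion.** The inconsistency is in the text: two analyses adjust for baseline alone, although allocation is stratified by center and the neighboring models include it. The consequence is conditional and runs in the conservative direction, with no bias and no inflation of false positives. If center explains 5% to 10% of residual variance, the reported standard error is about 2.6% to 5.4% too large and a nominal 5% test runs at about 4.4% to 3.9%. If it explains none, nothing is lost.

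These figures rest on an assumed center effect, on near-complete balance within centers, and on the parametric model. They are not evidence that any comparison would be invalid. The omission deserves correction mainly because the comparison of the two programs is the one where a nonsignificant result could be misread as showing equal effectiveness.

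**What to change.** Add center as a covariate in the digital versus face-to-face ANCOVA at 2 and at 6 months. State that the nonparametric ANCOVA is stratified by center, both for the primary endpoint and for the 2-month secondary scales that inherit it. Every between-group comparison then uses the same baseline-plus-center adjustment.

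The cost is a change of wording in the SAP, which the article says will be validated before the database is frozen. Sample size, data collection and randomization are unaffected. With 3 centers the ANCOVA gives up 2 degrees of freedom: for two arms of 40, the residual degrees of freedom go from 80 − 3 = 77 to 80 − 5 = 75.
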